Body visualizer task [44]	To assess the ability to accurately estimate body size (body size discrepancy) as well as the effects of sound feedback on perceived body size. Participants will adjust the weight related dimension of the body of a 3D avatar displayed on the screen to correspond to their perceived body size. Accuracy will be calculated according to the formula (estimated/actual body size) × 100 also-called body perception index (BPI) [45]. Specifically, a negative value represents an underestimation, whereas a positive value represents an overestimation	X		X

Body weight will be measured to the nearest 0.1 kg/% by means of a calibrated digital body fat scale (Sinocare CW 286). The Body feelings questionnaire will be directly built into Google Form and completed on a 10.1″ Android tablet (Lenovo M10)

^†^Spanish Version of the Eating Disorder Examination Questionnaire [46]

^‡^Spanish version of the Highly Sensitive Person Scale [47]

^§^The Multidimensional Assessment of Interoceptive Awareness [48]

Inclusion criteria will be: (a) normal (or corrected) auditory acuity; (b) sex: females (sex assigned at birth); (c) females within the healthy range of BMI (between 18.5 and 24.9) in order to reduce the likelihood of medical comorbidities that could affect the results (according to the World Health Organization index (WHO) [49]). Nevertheless, we recognize that weight/body mass index is not the sole predictor of potential co-occurring medical conditions. By doing so, we also avoid a potential confounding variable reported by [24]. This is in line with the criteria of healthy participants usually used in the field of eating disorders and body illusions research (e.g., [16]). Exclusion criteria: (a) lifetime history or presence of any significant brain injury, neurological condition, auditory pathology; (b) lifetime history or presence of a mental illness measured by self-report measures and screening questions; (c) lifetime history of underweight or overweight; (d) current use of psychotropic drugs (e.g. antidepressants) or intake of recreational synthetic or natural drugs; (e) inability to understand Spanish; (f) inability to provide consent; (g) out of age range; (h) pregnant status.

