The experimenter will use the measurements on the back of the ruler to record the fingertip and knuckle positions, rounding to the nearest 0.5 cm. After each trial, the clips are relocated. After completing the practice task, the experimental block will begin. Participants will repeat the task for thirty trials. Each experimental tone will be presented ten times. The order of trials will be randomized across participants. Participants will be given the opportunity to rest after each 10 trials.

After the experimental block, participants will be asked to repeat the task for three more trials (one for each sound condition, their order randomized across participants), in order to collect self-report measures (questionnaire block). After each trial, participants will complete a questionnaire that assesses their subjective experience during the task [see Additional file 2].

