### Data management

#### Estimation of body position/size and confidence task

For both experiments, data from the 10 repetitions for each condition will be averaged. As a rule of thumb, for participants with one trial per condition excluded, data for that trial will be replaced by the mean value of the other nine trials for that condition (as in [25]). Conversely, participants with more than one trial per condition excluded, will be excluded from all analyses. Overall, data from trials exceeding three standard deviations from the mean group value will be excluded.

For Experiment 1, we will collect measures for estimated knuckle position and fingertip position, as well as level of confidence with each estimation. In addition, for each trial, the estimated knuckle position will be subtracted from the estimated fingertip position in order to calculate the estimated finger length (as in [25]). For Experiment 2, we will collect waist width estimations, as well as level of confidence with each estimation. For each trial, we will estimate the perceived waist width by averaging the two responses given by the participant (i.e., for the opening and closing aperture).

For each participant a total of 12 summary scores will be calculated [(knuckle position + fingertip position + finger length + waist width limits) × (3 feedback conditions: ‘ascendent’, ‘constant’, ‘descendent’)]. Similarly, a total of 12 summary scores for the confidence task will be calculated [(confidence knuckle position + confidence fingertip position + confidence finger length + confidence perceived waist width limits) × (3 feedback conditions: ‘ascendent’, ‘constant’, ‘descendent’)].

Data from Presentation® software (Version 18.0, Neurobehavioral Systems, Inc., Berkeley, CA, www.neurobs.com) will be recorded into a file in UTF-8 format. The file will be organized and imported into Microsoft Excel 2021 and subsequently into IBM SPSS Statistics version 28.0. Data generated associated with the anchor tasks and practice tasks will be disregarded.

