### Sample size considerations

As these analyses are intended to generate future confirmatory hypotheses, no sample size calculation was conducted. As Jones et al. [53] noted, sample size calculation may be of little value in early exploratory studies where there is a lack of previous research. In an exploratory study, the primary focus is on generating new research questions, identifying patterns and trends, and identifying potential areas for further research, rather than on testing a specific confirmatory hypothesis. As such, the sample size in an exploratory study may not be determined based on statistical power or precision and could be relatively small. Instead, the sample size may be based on the need to obtain a sufficient amount of data to allow for the exploration and identification of meaningful patterns and trends.

In this regard, a total of 100 participants (50 participants in each group) will allow us to gain an exploratory understanding between body perception and non-naturalistic auditory information in participants with subthreshold ED symptomatology. This sample size is the minimum recommended by Brysbaert [54] to seek differences between groups and is also between 30 and 150 participants, that is the sample size usually recommended in exploratory study designs with non-probability sampling [55]. To this end, and based on norms for the Spanish version of the Eating Disorders Examination Questionnaire (S-EDE-Q), we will screen approximately at least 450 young adult females [39].

Due to the limited sample size, we acknowledge that the statistical power for each of the hypotheses proposed in this study to detect differences between groups might not be sufficient according to the traditional standards in experimental psychology (effect size = 0.4, power = 0.80 and alpha value = 0.05) [54]. Therefore, the results should be taken with caution and should be contextualized within an exploratory framework. In case of meaningful results, the present exploratory study will provide the necessary foundation for a formal sample size calculation for a future confirmatory larger-scale study.

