### Statistical analyses

#### Primary aim: auditory-driven changes in body perception Baseline measures

To determine differences between the groups, analyses will be performed with a Student's t-test paired comparison (for normal distribution) or Wilcoxon tests (for non-normal distribution) for ED symptomatology (EDE-Q), interoceptive body awareness (MAIA), sensory-processing sensitivity (HSPS) and body size discrepancy (Body visualizer tool).

#### Experiment 1 and Experiment 2

For the estimations of body part position/size, confidence task and items from the body feelings questionnaires we will follow a 2 × 3 ANOVA within-between interaction repeated-measures design (see Table 2). Specifically, we will use non-parametric ANOVAs on aligned rank (ART) data, suitable for ordinal data, using the R package ARTool [56]. The ANOVAs will involve a group factor with 2 levels (subthreshold EDs and controls) and a feedback condition factor with 3 levels (‘ascendent’, ‘constant’, ‘descendent’). Prior the analysis, assumptions of independence, normality and sphericity will be checked. As in [24], we will include the degree of body size discrepancy as covariate in case of significant baseline differences. Appropriate post-hoc tests will be conducted in case of significant differences.

**Table 2 Tab2:** ANOVA 2 × 3 design

Group	Feedback condition		
	Ascendent	Constant	Descendent
Subthreshold EDs	Subthreshold EDs–Ascendent	Subthreshold EDs–Constant	Subthreshold EDs–Descendent
Controls	Controls–Ascendent	Controls–Constant	Controls–Descendent

For body size discrepancy, we will follow a 2 × 3 ANOVA within-between interaction repeated-measures design (see Table 3). The ANOVAs will involve a group factor with 2 levels (subthreshold EDs and controls), a time factor with two levels (baseline and post-experiment) and a feedback condition factor with 3 levels (‘ascendent’, ‘constant’, ‘descendent’).

**Table 3 Tab3:** ANOVA 2 × 2 × 3 design

Group	Baseline	Experiment		
		Feedback condition		
		Ascendent	Constant	Descendent
Subthreshold EDs	Subthreshold EDs Baseline	Subthreshold EDs Post-experiment Ascendent	Subthreshold EDs Post-experiment Constant	Subthreshold EDs Post-experiment Descendent
Controls	Controls Baseline	Controls Post-experiment Ascendent	Controls Post-experiment Constant	Controls Post-experiment Descendent

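### The aligned-rank ANOVA fixed for the centimetre estimates has no step for the continuous covariate planned in the same paragraph

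*Protocol article*

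**What the plan says.** All references are to the protocol article.

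- **Model and method.** Statistical analyses, Experiment 1 and Experiment 2, puts three kinds of outcome under one design: "For the estimations of body part position/size, confidence task and items from the body feelings questionnaires we will follow a 2 × 3 ANOVA", with group (2 levels) and tone (3 levels) as factors. The method is then fixed: "we will use non-parametric ANOVAs on aligned rank (ART) data, suitable for ordinal data".
- **Covariate.** The same paragraph continues: "we will include the degree of body size discrepancy as covariate in case of significant baseline differences".
- **Scale of the size outcomes.** In Experiment 1 the experimenter will "record the fingertip and knuckle positions, rounding to the nearest 0.5 cm"; the waist clips are read to the same resolution. Under Data management, "data from the 10 repetitions for each condition will be averaged". Finger length is a difference of two positions, and waist width is the mean of an opening and a closing response.
- **Scale of the covariate.** Table 1, Body visualizer task: "Accuracy will be calculated according to the formula (estimated/actual body size) × 100". This is a continuous index, with one baseline value per participant.
- **Later use.** Sample size considerations says that, if results are meaningful, the study "will provide the necessary foundation for a formal sample size calculation" for a confirmatory trial.

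**The concern.** ART is a procedure for crossed factors. The article commits to it for four outcomes measured in centimetres, gives as its reason a property that concerns ordinal data, and then adds a continuous covariate without saying how the two combine. If the groups differ at baseline, the article no longer determines the analysis of those outcomes, and the choice is made with the data in view. A published plan should close off that choice.

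A lesser point is that the ART test works on ranks, so the primary analysis does not itself return the centimetre contrast or interval that a later sample size calculation would need.

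**Working it through.** The plan states no figure for this point, so there is none to reproduce.

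**1. What ART does.** Let y be the 10-trial mean for one participant and one tone. The value aligned for each effect is:

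- group: (y − cell mean) + (group mean − grand mean)
- group × tone: (y − cell mean) + (cell mean − group mean − tone mean + grand mean)

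The aligned values are ranked, a factorial ANOVA is run on the ranks, and only the effect aligned for is read. Every term is a factor mean. A covariate x has no term, so its influence stays in the residual when ranks are formed.

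**2. Which effect the covariate touches.** On the centimetre scale write y(i,j) = μ + group + tone(j) + group×tone(j) + βx(i) + s(i) + e(i,j), with s(i) the participant effect. In a within-person difference between two tones, βx(i) cancels. The covariate therefore bears on the group main effect. It reaches the group × tone contrast only if the slope may differ by tone, leaving (β_j − β_k)x(i). The article plans no such term.

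**3. How often the branch is reached.** Assume an independent-groups t-test, two-sided 5%, n = 50 per group. The normal approximation is Φ(d√(n/2) − 1.96), with √(50/2) = 5.

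- d = 0.4: Φ(2.0 − 1.96) = Φ(0.04) = 0.516; exact t, 0.508
- d = 0.5: Φ(2.5 − 1.96) = Φ(0.54) = 0.705, or about 0.70

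Both d values are assumptions. The article cites 0.4 only as a general benchmark and gives no expected baseline difference.

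**4. Whether the choice matters once there.** A simulation used 3000 runs, 50 per group and 3 tones. Its inputs are all assumed: covariate SD 1, groups 0.6 SD apart on it, slope 0.7, between-person SD 0.7, within-person SD 0.5, and no group effect given the covariate. Rejection rates for the group test at 5% were:

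| Route | Rate |
|---|---|
| ART, covariate dropped | 0.50 |
| ART, covariate added after ranking | 0.055 |
| ANCOVA on the raw scale | 0.051 |

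The 0.50 is not a fault of ranking. Without the covariate the groups do differ, by 0.7 × 0.6 = 0.42. The SD of a participant's mean is √(0.7² × 1² + 0.7² + 0.5²/3) = √1.063 = 1.03, so d = 0.42/1.03 ≈ 0.41. An unadjusted raw-scale test would reject with probability about Φ(0.41 × 5 − 1.96) ≈ 0.53. The table shows that keeping or dropping the covariate can change the conclusion about group.

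**5. Centimetre effect.** In one simulated data set, multiplying the outcomes by 1, 2 and 5 gave group × tone contrasts of 0.38, 0.77 and 1.92 cm, while the ART F stayed at 3.98. The raw-scale F is also scale-free (4.80 throughout), but the raw-scale model also returns the contrast and its standard error.

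**The case against.** Several parts of the opposing case stand.

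- **A reader might infer that the analysis becomes impossible.** It does not. Adding the covariate after ranking gave an acceptable 0.055 in the simulation. It is, however, not the procedure named, and the article does not choose it.
- **A reader might infer that the tests of illusion strength and pattern (H2 to H4) are compromised.** As planned, the covariate is a participant-level main effect and leaves the group × tone contrast alone.
- **A reader might infer that the branch will probably be reached because H1 predicts a baseline difference.** H1 is labelled exploratory and allows for equal distortion in the two groups. The 0.51 and 0.70 are conditional on assumed differences.
- **A reader might infer that the study cannot yield a centimetre effect size.** Descriptive statistics plans means and SDs for parametric data, and processed data are promised on OSF. The article does not commit to contrasts, within-person SDs or intervals, and it switches to medians and IQRs for non-parametric data. The quantities would still be recoverable from the shared data.
- **ART on continuous outcomes is valid.** Suitability for ordinal data does not make it unsuitable for centimetre means; preferring a raw-scale model on that ground alone would be taste.

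It can also be said that handling a contingent covariate is detail for a fuller plan. That would hold if the article were silent. Here it names both the method and the covariate, and they do not fit together.

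**Conclusion.** The concern holds in a limited form. The article fixes a factor-only rank procedure for four centimetre outcomes and, in the same paragraph, a conditional continuous covariate that the procedure has no step for. If the condition is met, the analysis as named cannot be run, and its replacement is chosen after the data are seen. The consequence falls mainly on the group main effect. The size of that consequence rests on the simulation's assumed inputs, and the chance of meeting the condition is unknown. The missing centimetre contrast is a secondary weakness of the named test, not a loss of the information from the study. The sample size is unaffected.

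**What to change.** For fingertip, knuckle, finger length and waist width, prespecify a linear mixed model (or a mixed ANOVA/ANCOVA with sphericity correction) on the centimetre scale. Include group, tone, group × tone and baseline body size discrepancy as covariate. Report the group and group × tone contrasts in cm with 95% CIs. If the covariate's slope is to vary by tone, say so in advance, because only then does it affect the group × tone contrast.

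Keep ART for the ordinal questionnaire items and as an unadjusted sensitivity analysis for the cm outcomes. State that the ART analyses carry no covariate; otherwise the same conflict remains there. Name the method for the confidence scores too, since they are 10-trial means of a 7-point rating and fall in neither class.

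The cost is analysis wording only; no procedure, data collection or sample size changes. The downside is reliance on approximate normality of the 10-trial means, which the ART sensitivity analysis helps to check. The groups are not randomised, so the adjusted group contrast answers a different question from the unadjusted one and should be labelled as adjusted.

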Given the lack of research, the primary aim of this study is to elucidate the link between body perception and non-naturalistic auditory information in participants with subthreshold ED symptomatology, as compared to participants without ED symptomatology, using two body illusions. Our primary objective is to investigate the effect of artificial non-naturalistic sounds on the perceived size of a finger in healthy individuals. Previous research has found that this type of sound, which does not contain information on body size, can elicit changes in the perceived size of a finger in a phenomenon known as the 'auditory Pinocchio' illusion [25]. In the first study to report this illusion, it was found that when healthy participants pulled the tip of their right index finger with their left hand and an ascending pitch sound was presented concurrently, the participants both felt and judged their finger to be longer than when the pull was combined with a descending pitch or a constant pitch sound [25]. This illusion builds on the well-known association between changes in pitch and changes in height or size (for a review see [26]). This illusion focuses on a body part (finger) that is not emotionally salient, reducing therefore ‘contamination' by cognitive processes [27]. Nevertheless, given the clinical relevance of studying emotionally salient body parts as they play an essential role in BID [4], and in order to extend the aforementioned research [24], we will adapt the 'auditory Pinocchio’ illusion to a body part that is particularly salient from the emotional point of view for the majority of EDs, namely the waist. We expect that the illusion also occurs for the waist (horizontal position) as for the finger (vertical position) since besides the correspondence with height, pitch is also associated to physical size (at least in the visual domain): static high and low pitches are respectively associated to smaller and larger visual size [28], and ascending and descending pitches are respectively associated to growing and shrinking size [29]. This body of research holds the potential to provide experimental evidence supporting the development of novel therapies, which can target specifically the aforementioned distortions in the perception of sensory body signals, and ultimately BID (e.g., [30]).

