## Aim and hypothesis

### Primary exploratory aim: auditory-driven changes in body perception

The primary aim of this study is to gain an exploratory understanding of the influence on body perception of non-naturalistic auditory information in participants with subthreshold EDs symptomatology using two body illusions. The scarce literature on the topic precludes us from considering a confirmatory model. As a result, the following hypotheses are all descriptive–exploratory.

**Hypotheses 1 (H1)**: Participants with subthreshold ED symptomatology will differ from participants without ED symptomatology in their degree of body image distortion. This hypothesis is exploratory, as alternatively, both groups may show the same degree of distortion.

H1 is based on previous literature that has shown a conflicting set of results. While there is strong evidence to suggest that young females with ED symptomatology and individuals with EDs tend to overestimate their body size compared to control individuals, some evidence suggests that body image distortions are not specific to this population, implying that they can underestimate their body size [24] or even be as accurate as individuals without ED symptomatology [32].

**Hypotheses 2 (H2)**: Participants with subthreshold ED symptomatology will show stronger auditory-driven body illusions, compared to control individuals.

H2 is based on the traditional hypothesis in support of a stronger influence of external sensory signals, leading to stronger body illusions in people with and subthreshold EDs [15–17].

**Hypotheses 3 (H3)**: Participants with subthreshold ED symptomatology, as compared to without ED symptomatology, will present unusual patterns of results in the finger elongation or shrinking waist illusion, suggesting impairments in the integration of artificial auditory signals into their body image.

H3 hypothesizes that participants with subthreshold ED symptomatology, as compared to people without ED symptomatology, will present unusual patterns of results, that is, the perceived finger elongation or shrinking waist will not necessarily occur in the ascending pitch condition (or not only in that condition, as in [24]. The results will shed light on whether the alteration in the mechanisms integrating auditory signals into body image is present only to natural signals related to body weight/size (e.g., footsteps) or it is linked to any auditory signals.

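### H2 predicts a stronger finger illusion in the subthreshold group, but it is tested only through a two-degree-of-freedom group-by-tone interaction with gated, unnamed follow-ups; a single named contrast would answer it directly

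*Protocol article*

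**What the plan says.** The Aim and hypothesis section states H2 with a direction: "Participants with subthreshold ED symptomatology will show stronger auditory-driven body illusions, compared to control individuals". The Background says what the finger illusion is. In the first study of it, with an ascending tone, participants "felt and judged their finger to be longer than when the pull was combined with a descending pitch or a constant pitch sound". H3, in the same section as H2, concerns unusual patterns, in which "the perceived finger elongation or shrinking waist will not necessarily occur in the ascending pitch condition".

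For body position and size, Statistical analyses (Experiment 1 and Experiment 2) names a 2 × 3 within-between repeated-measures design, run as an aligned-rank ANOVA: "The ANOVAs will involve a group factor with 2 levels (subthreshold EDs and controls) and a feedback condition factor with 3 levels". On follow-up it says: "Appropriate post-hoc tests will be conducted in case of significant differences".

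The 12 summary scores per participant listed under Data management are averages for each measure under each tone. None is a difference between tones. The only other analysis relating these measures to symptoms under the primary aim is a correlation with EDE-Q scores over the whole sample.

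**The concern.** H2 is a statement about one quantity: how much longer the finger is judged under the ascending tone than under the other two, compared between groups. The interaction test asks something wider, namely whether the three tone means run parallel in the two groups. It responds to a stronger illusion, to a weaker one, and to a difference between constant and descending that does not involve the ascending tone.

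Three things are at stake.

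- A significant interaction does not by itself tell H2 from H3, although the study sets the two against each other.
- The F test yields no estimate of the group difference in illusion strength. Sample size considerations says meaningful results should provide the basis for a formal sample size calculation for a larger confirmatory study, and such a calculation needs that estimate and its uncertainty.
- Running follow-ups only after a significant result can cost power in a study that already says its power may be insufficient.

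**Working it through.** **Figure in the plan.** There is no power figure to reproduce. Sample size considerations gives 50 per group, says that no calculation was made, and cites a benchmark of effect size 0.4, power 0.80 and alpha 0.05.

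**Inputs.** n = 50 per group and alpha = 0.05 come from the protocol. The SD and the within-person correlation are not given, so these are assumptions: effects are in SD units of the stated difference score, data are normal, and sphericity holds. Effects of 0.4 SD (the cited benchmark) and 0.5 SD are shown. The planned aligned-rank version was not simulated.

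**Degrees of freedom.** Interaction: (2 − 1)(3 − 1) = 2. Error: (100 − 2)(3 − 1) = 196. For a single score compared between groups: 100 − 2 = 98.

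**Score.** C = ascending − (constant + descending)/2, for each participant.

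**Case A: only the ascending tone differs, by d SD of C.** The noncentrality of t is d√(n/2) = 5d. That of F is (n/2)d² = 25d².

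| d | t noncentrality | F noncentrality | Omnibus F(2,196) | Contrast t(98), two-sided |
|---|---|---|---|---|
| 0.4 | 2.0 | 4.00 | 41.0% | 50.8% |
| 0.5 | 2.5 | 6.25 | 59.6% | 69.7% |

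**Case B: graded profile (ascending up, constant unchanged, descending down), scaled to the same F noncentrality.** C then captures only √0.75 = 0.866 of the effect, so its noncentrality is 5d × 0.866: 1.73 at d = 0.4 and 2.17 at d = 0.5.

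| d | Omnibus | Contrast C, two-sided |
|---|---|---|
| 0.4 | 41.0% | 40.3% |
| 0.5 | 59.6% | 57.3% |

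**Case C: only constant versus descending differs, by 0.5 SD of that difference.** F has the same noncentrality, 6.25, so it rejects in 59.6% of studies by formula (59.2% in simulation). The group difference in C is zero, so the contrast rejects in about 5%.

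**Case D: the illusion is weaker in the subthreshold group by 0.5 SD of C.** The omnibus test rejects in 59.6%. The two-sided contrast rejects in 69.7%, with the estimate in the opposite direction to H2.

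**Gating.** At 0.4 SD, requiring a significant interaction first and then a significant contrast in the predicted direction reaches an H2 conclusion in about 38 to 39% of simulated studies, against 51% when the contrast is tested directly. Here the contrast matches the true profile.

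**The case against.** The strongest reply has four parts.

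- **Post-hoc tests exist, and nothing says that a significant interaction will be read as H2.** This stands. A reader might infer that the plan rejects for the wrong reason, but the protocol does not support that. The interaction can mislead only if the follow-ups are ignored. Those follow-ups are, however, unnamed and conditional on significance, so they fix no reading of H2 in advance and do not recover the lost power.
- **The power gain depends on the profile.** This stands too. The Background says that ascending exceeded both other tones; it does not say that constant and descending are equal. Under a graded profile the proposed score gains nothing. A reader might also infer that the contrast brings power to 80% at 0.5 SD, but that figure belongs to a one-sided test, which is not proposed here.
- **A two-sided contrast also rejects when the illusion is weaker.** Correct, as Case D shows. Direction must be read from the estimate.
- **All hypotheses are labelled exploratory, low power is disclosed, and an article may leave the choice of contrast to a fuller plan.** The label lowers the weight of the point. It does not remove it, because the article itself fixes the test and the gate, and these fit H3 better than H2.

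The interaction is a reasonable test for H3, and nothing here argues for dropping it.

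**Conclusion.** The point holds in a limited form. For H2 in the finger experiment, the named test does not separate the hypothesis from an H3-type pattern and does not estimate the quantity that H2 concerns. Gating follow-ups on it can lower the chance of an H2 conclusion. The firmest result is the constant-versus-descending case: 59 to 60% rejection against 5%. The power loss is about 10 percentage points if the group difference is confined to the ascending tone, and about nil if it is graded. All figures assume 50 per group, normal data and sphericity, and have not been checked for the aligned-rank test.

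A general claim that the plan is underpowered because of this test, or that it will wrongly conclude in favour of H2, would go beyond the protocol. This is a worthwhile improvement to an exploratory plan. It does not invalidate the study.

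**What to change.** Add to Statistical analyses, for H2 in Experiment 1:

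- For each participant, compute estimated finger length under ascending minus the mean under constant and descending.
- Compare this score between groups with one two-sided independent-samples test, or its rank analogue, whether or not the interaction is significant.
- Report the group difference with a 95% CI, and read H2 as supported only if the difference is in the predicted direction.
- Keep the 2 × 3 interaction as the test for H3.

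Apply the same score to the waist only after its expected direction is reconciled. The Background links ascending pitch to growing size, while H3 speaks of a shrinking waist under the ascending tone.

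The cost is a short addition to the text and one more named test per experiment. No new data are needed. Any gain in power depends on the true tone profile; the estimate and the fixed reading of H2 do not.
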